### Intervention content and delivery procedures

This section specifies the full content of the eight-week intervention, integrating the weekly developmental targets, daily MI-style micro-nudges, and dual-trigger micro-coaching dialogues. The primary purpose is to translate the theoretical arc into an operationalizable schedule of high-frequency developmental affordances that can be implemented within standard high school counseling environment while maintaining the strict methodological transparency required for rigorous outcome evaluation. As outlined in Table 1, the weekly architecture includes: (a) a thematic PYD-linked developmental objective; (b) daily AI-delivered micro-nudges (≤ 40 words); and (c) a synchronous 10–15-min counselor mini-session. Sample scripts for the MI-style nudges and the underlying algorithmic logic for the micro-coaching are detailed in the Appendix.

### Research design

The present study utilizes a feasibility-oriented outcome research design rather than a powered efficacy trial. The primary analytic purpose is to demonstrate whether an AI-augmented PYD delivery scaffold can be successfully implemented within standard school counseling environments. Furthermore, it seeks to observe whether the targeted micro–behavioral processes (awareness, micro–choices, regulation moves, prosocial micro-behaviors) the model is designed to generate occur under naturalistic conditions. Grounded in feasibility logic (de Boer et al., 2025), the primary inferential question is not whether the intervention outperforms existing protocols, but rather whether this model can be successfully implemented and whether it reliably produces mechanism-consistent enactments.

A mixed methodological structure is required because the targeted constructs, self-regulation and perceived social connectedness, have a dual ontological status: they exist simultaneously as trait markers (i.e., stable, longitudinal dispositions) and state performances (i.e., enacted, momentarily observable micro-behaviors). Quantitative data alone cannot verify state enactment; rather, process-embedded qualitative evidence is essential to determine whether actual behavioral practice occurred. Consequently, in this protocol, quantitative indices are utilized to capture directional change, while qualitative materials serve to continuously verify mechanism enactment in real time.

Quantitatively, the design combines a within-subject trait-level pre–post comparison with an embedded single-case AB probe. The sequence consists of a pre-intervention baseline (Phase A; Weeks −2 and −1) and an active intervention period (Phase B; Weeks 1–8). The two-week baseline was adopted. A minimum of 10 data points in Phase A provides a more stable trend estimate for Tau-U baseline correction and more clearly distinguishes pre-existing directional drift from intervention-related change. Throughout Phase B, state-level EMA micro-ratings (1–7 Likert scales) index continuously index momentary regulation states. Trait-level self-regulation and social connectedness are measured at pre- and post-intervention timepoints via the within-subject standardized mean difference (Cohen’s *d*). To rigorously capture the dynamics of the state-level micro-trajectories, data will be evaluated using Tau-U, a robust, best-practice non-overlap effect size optimized for AB sequences in single-case experimental design (SCED) methodology.

The qualitative strand consists of (a) weekly counselor fidelity logs and (b) brief, one-sentence reflective student notes. These materials are not narrative interviews; rather, they serve as real-time process-evidence. Therefore, the analytic objective is not to achieve thematic saturation, but to execute mechanism-alignment detection. Reflexive thematic analysis will be used to identify and verify whether developmental practice indicators outlined in Table 1 occurred within a real-world educational environment.

All reflective notes remain accessible to the counselor to preserve the core ethical principle of human relational containment. The AI system does not store raw text beyond the generation of summary logs. Data retention adheres strictly minimal-retention feasibility norms; export functions are disabled. No participant data or conversational data is used for model training or model improvement. Furthermore, no algorithmic action is permitted without the possibility of immediate human override; should emotional dysregulation signals emerge, counselors escalate the case in accordance with established institutional safeguarding protocols. In this design, the AI is never the locus of clinical decision; rather, it is the engine for prompt density. Human counselors retain absolute safeguarding authority and interpretive control.

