### Model definition

The model is conceptualized as a developmental delivery architecture wherein human counselors establish the relational frame and developmental arc, while AI system executes the high-frequency micro-dosage required for proximal skill enactment. Critically, this intervention does not conceptualize AI as a counselor analog, therapist substitute, or diagnostic component, but as a systemic dosage amplifier. Counselors maintain primary responsibility for relational containment, while the AI autonomously delivers the high-volume, micro–developmental practice opportunities that human counselors cannot feasibly scale. This approach is grounded in the developmental reality that self-regulation and social connectedness are not cultivated through episodic learning, but through continuous, real-world repetition. The architecture therefore mirrors the mechanisms of motor-skill acquisition: micro-practice → consolidation → transfer. This counselor–AI co-delivery framework makes this repetition feasible within standard school constraints.

The intervention is deployed throughout eight consecutive school weeks. Each week focuses on one thematic developmental objective (see Table 1) and offers a synchronous 10–15-min counselor mini-session. This mini session serves as a vital “anchor point,” grounding the week’s developmental target in a supportive relational context while allowing the counselor to check ecological fit, safety, and progress. The remainder of the weekly dosage is delivered digitally through daily MI-style micro-nudges (e.g., ≤ 40 words). The sequence is intentionally graded to build capacity over time: initial weeks emphasize foundational awareness and micro-choice recognition; intermediate weeks prioritize active skill application in real-life contexts; final weeks focus on value mapping, identity congruence, and future transfer. In essence, the intervention is paced not by superficial “topic rotation,” but through the cumulative scaffolding of practice complexity.

**Table 1 tab1:** Structured eight-week progression of developmental objectives and measurable indicators.

Week	Theme	Weekly skill focus	Measurable outcome wording	Measurement schedule
0				Weeks −2 to −1: Consent, demographics, BSCS/SSBS (pre), two-week daily EMA baseline (Phase A)
1	Awareness	Noticing internal states & situational triggers	Student(s) can label at least one emotional state + one situational trigger per day	

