## Method

### Setting and participants

The intervention is designed for implementationwithin mainstream high school counseling settings serving adolescents aged 14–18. This ecological frame is intentional. As a feasibility study, the sample size is determined by the need to evaluate implementation applicability and estimation precision rather than statistical power for clinical efficacy. A target sample of 40–60 students from routine school caseloads, is sufficient to yield narrow confidence intervals (CIs) for recruitment/retention/compliance and to visualize heterogeneous individual-level micro-trajectories within an authentic delivery context. Feasibility will be evaluated against four pre-specified operational thresholds: (a) a recruitment rate ≥ 70% of eligible students; (b) a retention rate of ≥ 80% (defined as completing both pre- and post-intervention trait measures); (c) a median EMA compliance of ≥ 60% for daily prompts (1–7 Likert scale) across Weeks 1–8; (d) an intervention fidelity of ≥ 75% (defined as weeks where all three checklist items are met). These thresholds were derived from established benchmarks in the feasibility and pilot trial literature (Billingham et al., 2013; Eldridge et al., 2016). The 70% recruitment and 80% retention rates are widely adopted as minimum indicators of a viable study pipeline for a subsequent full-scale trial. The 60% EMA compliance threshold reflects the empirically observed lower bound of acceptable ecological momentary data completeness in adolescent digital health studies (Shiffman et al., 2008); compliance below this level produces phase lengths insufficient for reliable Tau-U estimation. The 75% fidelity threshold is grounded in the intervention science literature’s recommendation that at least three-quarters of protocol sessions be delivered as specified before efficacy conclusions can be considered (Bellg et al., 2004). Together, these benchmarks ensure that a positive feasibility verdict is substantively meaningful rather than nominally so.

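### The primary question asks whether enactments are reliably produced, but the analysis named for it only detects whether they occurred; the 75% fidelity threshold covers the gap in part and is not tied to the question

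*Protocol article*

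**What the plan says.** - **The question.** In Research design, the primary inferential question is "whether this model can be successfully implemented and whether it reliably produces mechanism-consistent enactments". The sentence before it sets a softer aim: whether the processes "the model is designed to generate occur under naturalistic conditions". The Abstract also uses the softer form.
- **Which strand answers it.** The same section gives verification to the qualitative strand: "Quantitative data alone cannot verify state enactment; rather, process-embedded qualitative evidence is essential to determine whether actual behavioral practice occurred". That strand consists of the weekly counselor fidelity logs and one-sentence student notes.
- **The analysis.** Thematic analysis is used "to identify and verify whether developmental practice indicators outlined in Table 1 occurred within a real-world educational environment". Data analysis strategy adds that coding is deductive and anchored to the weekly objectives. Its result then enters a triangulation matrix, where agreement across strands is taken to confirm feasibility.
- **The nearest numerical rule.** Setting and participants pre-specifies "an intervention fidelity of ≥ 75% (defined as weeks where all three checklist items are met". The items are at least four nudges opened, at least one note submitted, and a described behavior.
- **The enactment item.** Measures asks in item 3 for a prosocial or regulatory behavior. Appendix B asks instead for a behavior that fits that week's objective.

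**The concern.** To say that a model *reliably* produces something is to say how often it does so across students and weeks. To say that it *occurred* is to say that it happened at all. The plan asks the first and analyses the second. The enactment half of the primary question could therefore be reported as verified, and counted towards feasibility in the triangulation matrix, when only a modest share of student-weeks showed enactment. A later controlled trial that builds on this study would need the frequency, and the named analysis does not produce it.

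**Working it through.** The plan gives no enactment rate, so there is no figure of its own to reproduce. The rates below are assumptions.

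**Inputs**
- Students, N = 40 to 60: "A target sample of 40–60 students from routine school caseloads" (Setting and participants).
- Weeks = 8: "The intervention is deployed throughout eight consecutive school weeks" (Model definition). This gives 40 × 8 = 320 to 60 × 8 = 480 student-weeks.
- Table 1 has one indicator per week, so each indicator has N student-weeks.
- q = assumed chance that a student-week shows that week's indicator; student-weeks taken as independent.

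**Step 1. How easily can the occurrence standard be met?**

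One week's indicator seen at least once: 1 − (1 − q)^N. All eight seen at least once: [1 − (1 − q)^N]^8.

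Example, q = 0.10 and N = 40: 0.9^40 = 0.0148; 1 − 0.0148 = 0.9852; 0.9852^8 = 0.89.

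| q | One indicator, N = 40 / 60 | All eight, N = 40 / 60 |
|---|---|---|
| 1% | 0.33 / 0.45 | 0.0001 / 0.002 |
| 2% | 0.55 / 0.70 | 0.009 / 0.059 |
| 5% | 0.87 / 0.95 | 0.33 / 0.69 |
| 10% | 0.985 / 0.998 | 0.89 / 0.99 |

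At 10%, only about 32 of 320 or 48 of 480 student-weeks would show enactment, yet every indicator would very probably be found.

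Independence does not drive this. At the other extreme, a fraction q of students enact every week and the rest never do. The chance that all eight appear is then 1 − (1 − q)^N: 0.87 / 0.95 at 5% and 0.985 / 0.998 at 10%, which is higher than under independence.

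**Step 2. How far does the fidelity threshold fill the gap?**

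A week with all three items met is a week with item 3 met, so the composite rate cannot exceed the item 3 rate. A composite of at least 75% implies item 3 in at least 75% of weeks. If the 75% is pooled over student-weeks and the true composite rate is 50%, the chance of reaching it is about 5 × 10⁻²⁰ (320) or less (480). Rare enactment fails this rule.

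The reverse does not hold. A composite of 50% is compatible with item 3 being met in anything from 50% to 100% of weeks, so the composite alone does not give the enactment rate.

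**Step 3. Does item 3 match Table 1?**

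In the Measures wording, item 3 does not correspond to the week 1 (noticing states and triggers), week 2 (choice points) or week 4 (social cues) objectives. The Appendix B wording follows whatever the week's objective is.

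**Step 4. What precision would a reported proportion have?**

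Wilson 95% intervals for an observed 75%, using effective size = 8N / (1 + 7 × ICC):
- ICC 0: 70.0–79.4% (320) and 70.9–78.7% (480).
- ICC 0.3 (assumed): 320 / 3.1 = 103.2 gives 65.9–82.4%; 480 / 3.1 = 154.8 gives 67.6–81.2%.

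These are usable, and they show why clustering must be allowed for.

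**The case against.** The strongest reply is that a pre-specified rate already exists. The fidelity logs are part of the qualitative strand, Measures describes them as direct evidence that the mechanism was enacted, and the 75% threshold fails if enactment is rare. This stands. A reader might infer that nothing in the plan could answer the enactment question negatively; Step 2 shows that the documents do not support that. Nor is a failed threshold uninterpretable, since the three items are recorded separately and the item 3 column can be read.

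A reader might also pool all student-weeks and argue that a 1% enactment rate is near-certain to be called verified: 1 − 0.99^320 = 0.96 and 1 − 0.99^480 = 0.99. No section says that a single occurrence anywhere is enough. Coding is anchored to weekly objectives and several indicators are stated per day. Read week by week, a 1% rate would almost never produce all eight indicators.

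Finally, this is a condensed article and tabulation detail may sit elsewhere. That is fair for denominators, but the article does state its standard, and that standard differs from the question. Nothing in the article links the threshold to the word *reliably*.

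**Conclusion.** The point holds as a mismatch between the primary question and the analysis named to answer it; it is not a missing safeguard. Detecting occurrence gives no frequency, and read indicator by indicator it is very likely to succeed at an enactment rate of about 10% (0.89–0.99) and fairly often at 5% (0.33–0.69). These figures rest on assumed rates, independent student-weeks, and a reading in which one occurrence per weekly indicator suffices, which the plan neither states nor excludes. The 75% threshold gives real but indirect protection: it bears another label, mixes enactment with two engagement items, and depends on an item with two wordings. The change is worth making before data collection, but the feasibility design does not fail without it.

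**What to change.** In Research design and Data analysis strategy, answer the enactment question with the proportion of student-weeks in which checklist item 3 is met.

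- Use the Appendix B wording in Measures as well, so that the item follows each week's Table 1 objective.
- Report the proportion overall and by week, separately from the three-item composite.
- Give a 95% confidence interval that allows for clustering within student, for example a bootstrap over students.
- State how weeks with no log are counted.

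No new cut-off is needed. Alternatively, reword the primary question to whether, and how often, enactments occur.

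The cost is a little more tabulation of data already recorded, and a headline that may be a modest percentage where the plan now expects a verification. One limit remains: item 3 needs one behavior per week, so it will not show whether the per-day indicators of weeks 1, 2, 4 and 5 were met daily.

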### Data analysis strategy

The analytical framework of this study is structured to evaluate three outcomes: (a) trait-level directional movement, (b) state-level micro-trajectory change, and (c) mechanism enactment evidence. These three analytical layers correspond directly to the theoretical dimensions the intervention engages in disposition, enactment, and meaning-in-use. To assess trait-level shifts, pre- and post-intervention changes in the BSCS and SSBS will be quantified using a within-subject standardized mean difference, following Lakens’s (2013) generalized within-subject effect size formulation. This approach mitigates dependence on between-subject variability and is appropriate for feasibility designs wherein each participant serves as their own baseline control (Lakens, 2013, 2017). To robustly index the magnitude of directional movement, 95% confidence intervals will be calculated, despite traditional null-hypothesis significance testing not being required under feasibility logic.

State-level EMA sequences (Phase A baseline vs. Phase B intervention) will be analyzed using Tau-U with baseline trend correction. Importantly, correcting for baseline trend prevents inflated effect-size estimates that might otherwise be misattributed to intervention exposure rather than pre-existing directional drift. Tau-U allows non-overlap evaluation even with small samples and is currently the most methodologically defensible effect-size metric for SCED micro-regulation sequences. Qualitative data will be evaluated via reflexive thematic analysis, though explicitly restricted to mechanism verification rather than narrative phenomenology. Coding will be deductive and anchored to the weekly objective architecture.

Finally, to integrate the three evidence streams, a triangulation matrix will be constructed to map (a) trait-level shifts, (b) state-level effect estimates, and (c) qualitative mechanism evidence. The purpose of this synthesis is not to blend subjective narrative with statistical data, but to evaluate whether the targeted mechanism signal is reliably detectable across heterogeneous measurement modes. Methodological convergence across these domains confirms intervention feasibility, while signal divergence indicates a structural implementation malfunction.

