### Limitations

Given its architecture as a feasibility design, this study cannot causally attribute observed changes to the intervention, nor does it make any statistical inference regarding comparative superiority or clinical efficacy. Any observed trait- or state-level shifts may be confounded by normative developmental maturation, placebo engagement, social desirability, technological novelty effects, or seasonal artifacts of the school calendar. Furthermore, the fidelity documentation is strictly designed to assess the mere presence of mechanism enactment, not the qualitative depth or mastery of the skill. Consequently, no estimates of generalizability are proposed or assumed.

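### The baseline-corrected A-versus-B Tau-U ignores the order of the intervention days, so it summarises the overall A–B difference and not the state-level trajectory it is said to capture

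*Protocol article*

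**What the plan says.** The Research design section sets out a "pre-intervention baseline (Phase A; Weeks −2 and −1) and an active intervention period (Phase B; Weeks 1–8") and gives Tau-U the task of describing what happens over time: "To rigorously capture the dynamics of the state-level micro-trajectories, data will be evaluated using Tau-U". The Data analysis strategy lists "b) state-level micro-trajectory change" as the second of three outcomes and names one analysis for it: "State-level EMA sequences (Phase A baseline vs. Phase B intervention) will be analyzed using Tau-U with baseline trend correction". The reason given for the correction concerns drift before the intervention only: "correcting for baseline trend prevents inflated effect-size estimates". Missing data handling adds that missed days are dropped and that high- and low-compliance students are contrasted descriptively. No Phase B trend term, weekly contrast or early-versus-late contrast is named.

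Two other places bear on time course. Model definition describes a graded programme ("initial weeks emphasize foundational awareness and micro-choice recognition; intermediate weeks prioritize active skill application in real-life contexts") whose effects are expected to build and accumulate over the eight weeks. Limitations lists "technological novelty effects, or seasonal artifacts of the school calendar" among the possible explanations of any shift.

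**The concern.** A statistic offered as a measure of trajectory has to respond to the order of the observations. If it does not, outcome (b) is not measured as described. A student whose ratings jump early and drift back to baseline can then score the same as one whose ratings climb steadily.

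The distinction matters in this protocol because it expects accumulation and also admits novelty, which would tend to appear early and fade. The state-level estimate feeds a triangulation matrix in which agreement across streams is read as confirming feasibility and disagreement as an implementation malfunction. An index blind to order puts sustained and fading change into that matrix as the same entry, although the daily data to separate them are already collected.

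**Working it through.** The protocol gives no figure for this point, so there is none to reproduce. The invariance is algebraic; the numbers only illustrate it.

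**Formula.** Let S_AB be the sum of sign(b − a) over all pairs of one Phase A rating a and one Phase B rating b. Let S_A and S_B be Kendall's S within each phase. The named variant is

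Tau-U = (S_AB − S_A) / (nA·nB).

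S_AB is a sum over all A–B pairs and does not depend on the order within B. S_A uses Phase A only. Permuting the Phase B days therefore changes neither term.

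**Inputs.** Phase A is two weeks and Phase B eight. The text does not say whether daily means calendar or school days, so both 14/56 and 10/40 were used. A third case, 10/34, takes the minimum of 10 baseline points and the 60% compliance threshold (0.60 × 56 = 33.6, about 34). The ratings are assumed values on the 1–7 scale.

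**Same Phase B ratings, rising and reversed.**

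| nA/nB | S_AB | S_A | Tau-U, rising | Tau-U, reversed | Phase B Tau, rising / reversed |
|---|---|---|---|---|---|
| 14/56 | 424 | −17 | (424 + 17)/784 = 0.5625 | 0.5625 | ±739/1540 = +0.48 / −0.48 |
| 10/40 | 182 | −1 | (182 + 1)/400 = 0.4575 | 0.4575 | ±367/780 = +0.47 / −0.47 |
| 10/34 | 129 | −1 | (129 + 1)/340 = 0.3824 | 0.3824 | ±219/561 = +0.39 / −0.39 |

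In the 14/56 case the rising series has weekly means from 4.0 in Week 1 to 5.7 in Week 8. A random shuffle of the same ratings also gives 0.5625. Over 1000 simulated 14/56 pairs, the largest difference between rising and reversed order was exactly 0.

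**Simple deterministic case.** Take a constant baseline, half of Phase B above it and half equal to it. Then S_AB = 14 × 28 = 392, and 392/784 = 0.50, whether the raised half is Weeks 1–4 or Weeks 5–8.

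**Noisy case** (assumed baseline mean 4, SD 1, effect 1.5 points). An effect fading linearly to 0 and one building from 0 both average 0.36 on the pooled index. Tau against Phase A for Weeks 1–2 / 3–5 / 6–8 reads 0.62 / 0.41 / 0.14 for the fading course and 0.10 / 0.32 / 0.57 for the building one. A repeat simulation agreed to within about 0.01.

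**Other members of the Tau-U family.**
- Adding the Phase B trend, (S_AB + S_B − S_A)/(nA·nB + nA(nA−1)/2 + nB(nB−1)/2), separates the two orders. At 14/56 this is 1180/2415 = +0.49 rising and −298/2415 = −0.12 reversed.
- The Theil–Sen baseline-corrected Tau is not strictly order-invariant when the baseline slope is non-zero. That occurred in 15% of simulated flat baselines, and the mean rising-minus-reversed difference was about −0.01. It does not measure Phase B shape either.

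**The case against.** **The variant may be settled elsewhere.** Tau-U is a family, and a condensed article can leave details to an analysis plan. The point does not rest on a missing detail: the article names a variant, justifies it by baseline drift only, and states that it captures dynamics, which that variant does not do.

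**Other strands cover timing.** Research design gives the quantitative indices the role of directional change and leaves real-time verification of the mechanism to weekly logs and student notes. Setting and participants also mentions visualising individual trajectories. Both soften the consequence, since a fade could be seen or noted. But visualisation appears only as a sample-size reason, no step in the Data analysis strategy uses it, and outcome (b) is still labelled trajectory change.

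**Causal attribution is already disclaimed.** This stands. Without a control arm, a rising profile also fits maturation or school-calendar drift, and an early peak may be a real response that was not sustained.

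**Stronger readings that the documents do not support.**
- A reader might infer that the protocol predicts a flat EMA item in Weeks 1–2 and a rise from Week 3. It does not. Table 1 grades curriculum content, the text speaks only of building and accumulating, and awareness and micro-choices could plausibly move the item early.
- A reader might infer that an early peak that declines demonstrates novelty. The design cannot show that.
- A reader might infer that, with no effect in Weeks 1–2 and complete separation afterwards, the pooled index is capped at 42/56 = 0.75. For the corrected index this is false, because a declining baseline makes S_A negative. With a baseline of seven 4s then seven 3s, Weeks 1–2 identical to it and all 7s afterwards, S_AB = 14 × 42 = 588 and S_A = −49, so Tau-U = 637/784 = 0.8125.

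**Conclusion.** The point holds in this form. The named statistic measures the overall A–B difference and is exactly invariant to the order of the Phase B days. It cannot deliver the trajectory outcome or tell a fading change from a building one. This needs only one assumption, that the variant is the one the text names (A versus B less the baseline trend). The illustrative sizes, such as 0.36 for both courses with opposite block profiles, rest on assumed ratings.

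The consequence is moderate. None of the four feasibility thresholds uses Tau-U, but the state-level estimate is one of three streams in the triangulation matrix, where sustained and fading change would be indistinguishable.

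**What to change.** 1. In Research design and Data analysis strategy, describe the pooled Tau-U as a summary of the overall A–B difference rather than a measure of dynamics.
2. Pre-specify one descriptive Phase B time-course measure from the daily ratings: either a Kendall Tau within Phase B, or Tau against Phase A for early, middle and late blocks that follow the stages in Table 1. Weeks 1–2, 3–6 and 7–8 is one reading of those stages.
3. Carry that measure into the triangulation matrix beside the pooled value.
4. State the interpretation in advance: a rising or sustained profile is consistent with build-up; an early peak that declines is consistent with novelty or an unsustained response. Neither is proof.

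**Cost.** Wording and a few more computed values per student; no new data. The drawback is precision. At 60% compliance on school days, Weeks 1–2 yield 0.60 × 10 = 6 ratings. Under the assumptions of the noisy case, the per-student SD of that block's Tau for the building course is about 0.3 around a mean below 0.1. Block values should therefore be summarised across students and not used to classify individuals.
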